# Estimated oxygen extraction versus dynamic parameters of fluid-responsiveness for perioperative hemodynamic optimization of patients undergoing non-cardiac surgery: a non-inferiority randomized controlled trial

**DOI:** 10.1186/s12871-020-01011-z

**Published:** 2020-04-18

**Keywords:** Perioperative goal directed therapy, Fluid-responsiveness, Oxygen extraction rate, Complications

## Abstract

**Background:**

Goal directed therapy (GDT) is able to improve mortality and reduce complications in selected high-risk patients undergoing major surgery. The aim of this study is to compare two different strategies of perioperative hemodynamic optimization: one based on optimization of preload using dynamic parameters of fluid-responsiveness and the other one based on estimated oxygen extraction rate (O_2_ER) as target of hemodynamic manipulation.

**Methods:**

This is a multicenter randomized controlled trial. Adult patients undergoing elective major open abdominal surgery will be allocated to receive a protocol based on dynamic parameters of fluid-responsiveness or a protocol based on estimated O_2_ER. The hemodynamic optimization will be continued for 6 h postoperatively. The primary outcome is difference in overall postoperative complications rate between the two protocol groups. Fluids administered, fluid balance, utilization of vasoactive drugs, hospital length of stay and mortality at 28 day will also be assessed.

**Discussion:**

As a predefined target of cardiac output (CO) or oxygen delivery (DO_2_) seems to be not adequate for every patient, a personalized therapy is likely more appropriate. Following this concept, dynamic parameters of fluid-responsiveness allow to titrate fluid administration aiming CO increase but avoiding fluid overload. This approach has the advantage of personalized fluid therapy, but it does not consider if CO is adequate or not. A protocol based on O_2_ER considers this second important aspect. Although positive effects of perioperative GDT have been clearly demonstrated, currently studies comparing different strategies of hemodynamic optimization are lacking.

**Trial registration:**

ClinicalTrials.gov, NCT04053595. Registered on 12/08/2019.

## Background

Any surgical intervention is a trauma for the organism and a stress response is activated to cope the external insult. This stress response is responsible of an increase in oxygen consumption. Shoemaker et al. [1] showed that oxygen debt start intraoperatively in high risk surgical patients. If patient is not able to overcome the deficit in oxygen consumption (VO_2_) during the first hours postoperatively, he/she will go toward complications (in case of delay to meet metabolic demand) or death (in case of persistent VO_2_ deficit). The same authors showed that the incidence of organ failure and mortality were reduced when oxygen debt was rapidly compensated using a protocol of hemodynamic optimization aiming to reach the same hemodynamic targets recorded in survived patients [1]. Therefore, several protocols have been developed to optimize hemodynamic parameters with the aim to reduce tissue hypoperfusion coming from maldistribution or inadequate perfusion and meet the increased metabolic need as soon as possible.

Every patient that probably will not be able to face the surgical stress himself might benefit from modulation of hemodynamic parameters. Actually, goal directed therapy (GDT) is able to improve survival only in high-risk surgical patients [2]. On the other hand, the reduction of complications rate has been shown also in intermediate-risk population [3–7].

Originally, hemodynamic optimization protocols were developed to reach supranormal value for cardiac output (CO) and oxygen delivery (DO_2_) [1]. DO_2_ is locally regulated according to tissue metabolism and an adequate global DO_2_ may coexist with local hypoperfusion. An inadequate regional DO_2_ is responsible for an increase of oxygen extraction, a reduction of mixed venous oxygen saturation (SvO_2_) and central venous oxygen saturation (ScvO_2_) as its surrogate and finally an increase of lactate. Based on the concept that oxygen extraction rate (O_2_ER) reflects the balance between DO_2_ and VO_2_, a GDT protocol based on O_2_ER estimation (O_2_ERe) calculated as (SaO_2_-ScvO_2_)/SaO_2_ (where SaO_2_ is arterial oxygen saturation) has been proposed showing a significantly lower number of organ failure postoperatively compared with control group [8].

The major determinants of DO_2_ are CO, hemoglobin (Hb) level and SaO_2_. An inadequate CO may be optimized using fluids as first line therapy and then inotropes. In mechanically ventilated patients, heart-lung interaction is useful to recognize in which portion of the Frank-Starling curve the heart of the patient is working and then if CO is able to rise after fluid administration aimed to increase preload. Several parameters based on mini-invasive monitor systems are available to assess fluid responsiveness such as pulse pressure variation (PPV) and stroke volume variation (SVV) [9]. Optimization of functional parameters allows titration of fluid administration and personalization of therapy for each patients [10]. Thus, several perioperative GDT protocols are based on fluids administration as long as PPV or SVV is above a pre-defined cut-off, aiming to preload maximization.

Although positive effects of perioperative GDT have been clearly demonstrated, currently studies comparing different strategies of hemodynamic optimization are lacking. To date, only one trial investigated the effect of a protocol based on O_2_ERe [8], whereas many studies were based on functional parameters of fluid-responsiveness (PPV or SVV). Thus, we believe useful a trial comparing different strategy of hemodynamic optimization.

## Methods/design

The protocol adheres to the Standard Protocol Items: Recommendations for Interventional Trials (SPIRIT) 2013 guidelines [11].

### Study aim

The aim of the study is to compare a perioperative hemodynamic optimization protocol based on O_2_ERe referred to a protocol based on normalization of dynamic parameters of fluid-responsiveness (PPV or SVV).

### Objectives

The primary objective is to evaluate the difference in developing overall complications during hospital stay between the two group of patients managed with two GDT protocols using a non-inferiority approach.

The secondary outcomes are the difference between the total amount of fluid administered, the total fluid balance, the needs of vasopressor/inotropes, the hospital length of stay and the mortality at day 28.

### Study design and setting

This is a multicenter randomized controlled trial. As both PGDT protocols showed to reduce postoperative complications compared to standard therapy and they are routinely applied for this kind of patients in common clinical practice [8, 12], a non-inferiority trial will be performed as the effect on primary outcome is expected to be maintained in both groups and it does not seem reasonable for ethical reason to deprive a study group of an established strategy for hemodynamic management during perioperative period. The study will be performed in 15 centers in Italy (Additional file 1).

### Subjects and study population

#### Inclusion criteria

Adult patients (age > 18 years) undergoing to general anesthesia and mechanical ventilation for elective major open abdominal surgery (gastrointestinal, urologic, gynecologic and vascular surgery)Expected duration of surgical procedure higher than 120 minASA-PS Classification II-III-IVPlanned postoperative ICU/HDU admission

#### Exclusion criteria

PregnancyCardiac arrhythmiaNon-correctable arterial curve alterationsUndergoing palliative surgeryDenial of consent to participate

### Randomization

After screening for inclusion and exclusion criteria, patients suitable to be enrolled will be allocated with 1:1 ratio to randomly receive one of the two protocol of perioperative hemodynamic optimization. A computer-based system will be used to create a block randomization list (block size of 6). The allocation sequence concealment will be guaranteed by sealed opaque envelopes. Patients and researchers that perform postoperative follow up will be blinded to the allocated protocol.

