### Sample size calculation

From literature analysis, we estimate a complication rate for control and experimental group of 28 and 35% respectively [2, 15]. With a non-inferiority margin of 10%, 184 patients (92 for each group) are needed to have a power of 80% and an alfa error of 0.05 [16]. Considering a 10% losing in follow-up, we enroll 200 patients (100 for each group).

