## Discussion

The role of perioperative hemodynamic optimization has been clearly shown by literature and the current spreading of mini-invasive monitoring systems able to estimate CO permits an easier application of these protocols than occurring in the past when only invasive techniques (e.g. pulmonary artery catheter) were available. As a predefined target of CO or DO_2_ seems to be not adequate for every patient, a personalized therapy is likely more appropriate. Following this concept, dynamic parameters of fluid-responsiveness (PPV and SVV) allow to titrate fluid administration aiming an increase of CO as a consequence of preload optimization but avoiding fluid overload. This approach has the advantage of personalized fluid therapy, but it does not consider if CO is adequate or not because preload optimization occurs independently from parameters of tissue perfusion and oxygen consumption. A protocol based on O_2_ER considers this second important aspect. An O_2_ER higher than a predefined cutoff is reflecting an inadequate DO_2_ to tissue and consequently an inadequate CO. This condition, but not fluid-responsiveness per se, is the trigger to start hemodynamic optimization. Moreover, in this contest we believe that CVP may be useful to limit fluid administration independently from PPV or SVV value. In fact, CVP depends on several conditions including preload status but also on cardiac function and ventricular compliance. Thus, this trial aims to demonstrate that this latest strategy of perioperative hemodynamic optimization is not inferior to the former in term of postoperative complications, but it may be responsible for a lower fluid administration. We decided to conduct a non-inferiority study because PGDT is routinely applied in this kind of patients due to the demonstrated benefits on outcome. Thus, small difference in reduction of postoperative complication rate between two different PDGT protocols seems reasonable.

Methodologically, the main limitation of this trial is the inability to blindly administer the interventions. However, this point is not clinically resolvable in this research field. Moreover, if participation of several centers may increase enrollment rate and may potentially extend the applicability of results, on the other hands too few patients per center may increases heterogeneity.

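### A single published block size of 6, with unblinded treating staff, makes up to a quarter of allocations deducible in advance if lists are held per centre

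*Protocol article*

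**What the plan says.** The Randomization section of the protocol article gives one scheme. On the sequence: "A computer-based system will be used to create a block randomization list (block size of 6"). On the ratio: "patients suitable to be enrolled will be allocated with 1:1 ratio to randomly receive one of the two protocol of perioperative hemodynamic optimization". On concealment: "The allocation sequence concealment will be guaranteed by sealed opaque envelopes". No second block size and no random variation of size is mentioned.

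On blinding, the same section states: "Patients and researchers that perform postoperative follow up will be blinded to the allocated protocol". The Discussion concedes that "the main limitation of this trial is the inability to blindly administer the interventions".

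On scale, Study design and setting says "The study will be performed in 15 centers in Italy", and Sample size calculation says "Considering a 10% losing in follow-up, we enroll 200 patients (100 for each group").

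The Trial status section reports that patients were still being recruited when the manuscript was submitted, with completion expected by December 2021. The article appeared in April 2020.

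The article does not say whether there is one list or one per centre, or who holds and opens the envelopes.

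**The concern.** Permuted blocks of constant size have a known weakness. Once the block size is known and earlier allocations in the block have been seen, the last allocations follow by subtraction. Three conditions make that usable, and the article documents two of them: the size is constant and public, and the people delivering the haemodynamic protocol know which protocol they are delivering. The third, a list confined to one centre, is plausible with paper envelopes at 15 sites but is not stated.

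What is at stake is selection at enrolment. Surgery is elective, so the moment of enrolment may be adjustable. Some entry criteria rest on judgement, such as the anticipated length of the operation and the plan for intensive or high-dependency care afterwards. ASA classes II to IV cover a wide range of risk. A recruiter who knows the next allocation could hold back or bring forward a particular patient. Blinded follow-up protects the assessment of complications but does nothing about who enters which arm. The primary comparison described is a Fisher or chi-square test with a confidence interval for the difference, neither of which would correct for such a shift.

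**Working it through.** The plan gives no figure of its own for predictability, so there is none to reproduce.

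**Inputs.** Block size 6 and ratio 1:1 (Randomization); 15 centres (Study design and setting); 200 patients (Sample size calculation). Assumptions: one list per centre, equal recruitment across centres, and an observer who has seen every earlier allocation from that list.

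**Step 1: allocations that are certain within one block.** A 3:3 block can be ordered in C(6,3) = 20 ways. An allocation is certain when one arm has already used its three places.

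| Position in block | Orderings in which it is certain | Probability |
|---|---|---|
| 1 to 3 | 0 of 20 | 0 |
| 4 | 2 of 20 | 0.10 |
| 5 | 8 of 20 | 0.40 |
| 6 | 20 of 20 | 1.00 |

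Expected number per block: 0.10 + 0.40 + 1.00 = 1.5, and 1.5/6 = 25%.

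**Step 2: scale to the trial.** 200/15 = 13.3 patients per centre, for example ten centres of 13 and five of 14 (130 + 70 = 200). Each centre completes two blocks (12 patients) and starts a third with one or two patients, whose positions are never certain. Expected certain allocations: 15 × 2 × 1.5 = 45, and 45/200 = 22.5%. If centre totals instead vary at random around an equal expected size, the figure is about 42. So 25% is the ceiling, reached only with complete blocks.

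**Step 3: effect of varying the block size.** Simulation with 12 patients per centre and equally likely sizes. The observer is assumed to know the set of possible sizes and to track every allocation, which is the worst case for the remedy.

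| Block sizes | Certain in advance | Best guess correct |
|---|---|---|
| Fixed 6 | 25% | 68% |
| 4, 6 | 6% | 68% |
| 2, 4, 6 | 3% | 69% |
| 4, 6, 8 | 2% | 66% |

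The exact value for the best guess in a fixed block of 6 is 4.1/6 = 68.3%. With 13 patients per centre, certainty for fixed 6 is 23% and the other certainty figures are essentially unchanged. At 2%, certain allocations across 200 patients would number about 4, against about 45.

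**Step 4: what steering could do (illustration only).** Suppose every deducible slot were steered, so that the baseline complication risk of patients in those slots differed between arms by 10 to 20 percentage points. Both suppositions are assumptions and the first is extreme. The observed difference would move by 0.225 × 10 = 2.25 to 0.225 × 20 = 4.5 points, against a margin of 10 points. Partial steering scales this down in proportion.

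**The case against.** The strongest reply is that the harm is conditional. The article condenses a fuller protocol, and the scope of the list and the handling of envelopes are details it may reasonably leave out. It shows that the treating clinician knows the current patient's arm. It does not say that recruiters know all earlier allocations, or that recruiters and treating anaesthetists are the same people. Computer-generated permuted blocks with sealed opaque envelopes are an accepted method. Both strategies are described as routine and beneficial, so the motive to steer patients is weaker than with an untreated control. All of this stands, and it limits the point to a conditional one. It does not remove the point, because the constant block size and its publication are stated facts.

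Several stronger readings are tempting but unsupported:

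- A reader might infer that the trial is open-label throughout. It is not: patients and follow-up researchers are blinded, and the risk rests on the treating and recruiting staff.
- A reader might infer that a single list shared across centres would be equally faulty, since it would leave arms unbalanced within small centres, and might cite the Discussion's remark that "too few patients per center may increases heterogeneity". The article does not say that such a list is used. Imbalance within centres costs comparability and precision but is not itself a bias.
- A reader might multiply 25% by 200 and report 50 predictable patients. That treats every block as complete; at 13.3 patients per centre it is about 45.
- A reader might present the 68% success rate of an educated guess as a harm that varying the block size would cure. It would not: the rate stays at 66% to 69%.

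**Conclusion.** The point holds in conditional form. With per-centre lists, a constant and published block size of 6 lets staff who recruit and track earlier allocations deduce at most 25% of allocations with certainty. That is about 45 of 200 if the 15 centres recruit equally, and about 42 if their totals vary at random. The result rests on three assumptions: per-centre lists, full knowledge of past allocations, and equal expected recruitment. If the full protocol shows one list run across all centres, deduction would require knowledge of allocations at other sites, and the point loses most of its force.

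This is an avoidable opening for selection bias and not evidence of bias. The document neither contradicts itself here nor shows that any allocation was anticipated. It is best treated as a cheap improvement.

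**What to change.** First confirm from the full protocol whether lists are per centre and who holds the envelopes. For patients not yet randomised, issue computer-generated lists per centre with randomly varying block sizes, for example 4, 6 and 8, and do not disclose the sizes to sites. Keep the sealed opaque envelopes. In the amendment, state only that block sizes vary at random; the sizes can be reported after recruitment closes.

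The cost is new lists and envelopes and a short amendment. There is slightly more room for arm imbalance from incomplete blocks: a centre that stops mid-block can be out by at most half the block, so 4 patients with a block of 8 against 3 with a block of 6. Blocks cut short at the changeover add to this. The sample size does not change. The amendment should not claim that guessing is prevented, only that certainty is largely removed.

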### General care and procedures

Patients undergoing elective non-cardiac surgery will be screened to participate to the study. They will be enrolled and allocated to one of the two groups if they meet all inclusion criteria and none of exclusion ones. All patients will be undergone to general anesthesia and mechanically ventilated with a tidal volume of 8 ml/kg and a positive end expiratory pressure (PEEP) of 5 cmH2O. FiO_2_ will be set at discretion of attending anesthesiologist to maintain normoxia. An arterial cannula will be used for continuous arterial monitoring. The arterial transducer will be zeroed at the level of the fourth intercostal space in the middle axillar line. The square-wave test will be used to assess the presence of over−/under-dumping on the arterial signal. A CO monitoring system will be used to record hemodynamic parameters. A central venous catheter will be placed after induction of anesthesia. A balanced crystalloid solution at the rate of 1 ml/kg/h will be administered intraoperatively. Any further fluid bolus will be administered according to the protocol in which the patient is allocated. Balanced crystalloid solutions are the only fluids permitted. Packed red blood cells will be transfused to maintain Hb ≥8 g/dl, at discretion of attending anesthesiologist. Mean arterial pressure will be maintained between 60 and 100 mmHg modulating anesthetic drugs on surgical stimulus or using vasopressor/vasodilator drugs, at discretion of attending anesthesiologist.

### Protocol a

Patients allocated to protocol A will received a GDT protocol based on dynamic parameters of fluid-responsiveness for optimization of fluid status (Fig. 1). Dobutamine will be used with discretion of the attending anesthesiologist as clinically needed. The protocol will be continued postoperatively up to 6 h when dynamic parameters remain applicable (controlled mechanical ventilation, absence of arrythmia, etc.). On the other hand, fluid challenge technique with 250 ml of crystalloid over 5 min will be used for fluid optimization considering 10% increase in CO as positive response.

**Fig. 1 Fig1:**
[figure not shown]
Protocol A: Hemodynamic optimization protocol based on dynamic parameters of fluid responsiveness. PPV: pulse pressure variation; SVV: stroke volume variation

PPV is calculated as:
$$ PPV\ \left(\%\right)=\frac{\mathrm{PPmax}-\mathrm{PPmin}}{\left(\mathrm{PPmax}+\mathrm{PPmin}\right)/2}X\ 100 $$where PP is pulse pressure.

SVV is calculated as:
$$ SVV\ \left(\%\right)=\frac{\mathrm{SVmax}-\mathrm{SVmin}}{\left(\mathrm{SVmax}+\mathrm{SVmin}\right)/2}X\ 100 $$where SV is stroke volume.

### Protocol B

Patients allocated to protocol B will received a GDT protocol based on O_2_ERe intraoperatively and for the first 6 h postoperatively (Fig. 2).

**Fig. 2 Fig2:**
[figure not shown]
Protocol B: Hemodynamic optimization protocol based on estimated oxygen extraction rate. CVP: central venous pressure; O_2_ERe: oxygen extraction rate estimate; PPV: pulse pressure variation; SVV: stroke volume variation

O_2_ER is estimated at the start of the surgery and then hourly as:
$$ O2 ERe=\frac{SaO2- ScvO2}{SaO2} $$where SaO_2_ is arterial oxygen saturation and ScvO_2_ is central venous oxygen saturation.

### Data collection

At randomization, demographic and clinical data will be recorded:
Age, sex, weight, heightAdmission diagnosisComorbidities (e.g. diabetes mellitus, chronic kidney injury, chronic obstructive pulmonary disease, cardiac dysfunction, etc.)

During perioperative period, main clinical parameters will be recorded:
Ventilation modality and parameters (spontaneous, assisted/controlled, tidal volume, respiratory rate, airway pressures, FiO_2_)Anesthetic/analgesic drugsHemodynamic parameters (blood pressure, heart rate, CO, SV, SVR, PPV, SVV)Arterial blood gasCentral venous blood gasFluids (crystalloids and colloids), transfusion and fluid balanceInotropic/vasoactive drugsDaily SOFA score

Finally, the following outcomes will be recorded:
Complication during hospital stay (Table 1)Hospital length of stayMortality at day 28

**Table 1 Tab1:** Complications assessed during postoperative period

Acute myocardial ischemia/infarction	Multiorgan failure
Cardiac arrhythmia	Delirium/psychosis
Cardiac/respiratory arrest	Urinary tract infection
Cardiogenic pulmonary edema	Bacteremia
Pulmonary embolism	Surgical site infection
Acute respiratory distress syndrome	Nosocomial pneumonia
Gastrointestinal bleeding	Unknow origin infection
Intestinal infarction	Stroke
Anastomotic leakage	Post-operative hemorrhage
Paralytic ileum	Surgical re-intervention
Acute kidney injury	

Severity of postoperative complications will be defined according to Clavien-Dindo classification [13]. Complication grades I and II will be considered as minor complications while grades III and IV will be considered as major ones.

The Case Report Forms (CRFs) will not bear the participant’s name or other directly identifiable data. The participant’s trial Identification Number (ID) only, will be used for identification.

The flow diagram according to CONSORT guidelines [14] is provided as Fig. 3. Figure 4 shows an overview of all outcome measures in accordance with SPIRIT guidelines [11].

